#### Ancillary and post-trial care {34}

All participants will continue to receive standard KS care at their treating institution regardless of study participation. There is no additional post-trial care obligation, as the study intervention (3D imaging) poses minimal risk. In the unlikely event that a participant suffers harm directly attributable to study participation, appropriate medical care will be provided at the study site at no cost to the participant.

### Outcomes {16}

#### Objective 1 (Reproducibility and Accuracy)

##### Primary outcomes:

(1) Concordance correlation coefficient (CCC) for inter-rater reproducibility of KS lesion area measurement. The CCC will be calculated separately for SS3D and for the ruler-based method, based on measurements by two independent clinicians of the same three lesions per participant. The measurement variable is projected lesion area (mm^2^). The method with the higher CCC will be considered the more reproducible. (2) Coefficient of determination (R-squared) for each measurement method, assessing the proportion of variation attributable to true lesion size versus random measurement error.

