### Sample size {19}

Objective 1: Assuming that the mean and variance of the area of lesions (as determined by the SkinScan3D method) are the same for two clinicians, then the expected width of a 95% confidence interval (CI) for the concordance correlation coefficient for a given number of lesions examined is shown in Table 1. Therefore, with at least 50 participants with 3 lesions each (150 lesions), we will get a precise estimate of the CCC. To address overinterpretation of the concordance, we will complement the R-squared with additional metrics that capture accuracy more directly, including Bland-Altman plots to assess agreement and systematic bias, mean absolute error, and root mean square error. These measures will allow us to evaluate both correlation and the magnitude and direction of differences between methods.

Objective 2: We will roll out the refined SS3D intervention to 100 participants (50 patients at UCI; 25 at JOOTRH; 25 at Homa Bay). All providers will complete quantitative surveys. We anticipate recruiting providers (up to n=10), clinic administrators and key decision makers (up to n=5) who will participate in semi-structured interviews at each clinic. The final sample of semi-structured interviews will be determined by the point at which thematic saturation is achieved.

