### Statistical methods

Statistical methods for primary and secondary outcomes {27a}

#### Objective 1

We will plot a graph for each measurement method. Each graph’s x-axis will represent measurements from clinician 1 and y-axis will represent measurements from clinician 2. For each graph, we will calculate the concordance correlation coefficient (CCC) and coefficient of determination (R-squared). The CCC measures reproducibility (agreement) between clinicians for each method. The method with the higher CCC will be considered the more reproducible, and the method with R-squared closer to 1 will be considered the more accurate. We will also visualize agreement between methods graphically using Bland-Altman plots, and report the mean difference and 95% limits of agreement. To provide a more robust assessment, we will also report mean absolute error and root mean square error to capture the magnitude of differences between methods.

#### Objective 2

System Usability Scale (SUS) scores will be computed following standard scoring procedures (score contributions from items summed and multiplied by 2.5, yielding a score range of 0 to 100). Device usability will further be normalized to generate percentile ranks and graded as either acceptable (score above 68), marginal, or not acceptable. AIM, IAM, and FIM scores will be presented as means, standard deviations, and ranges. Qualitative data collected from semi-structured interviews will be transcribed, coded, and thematically analyzed to identify sub-themes and themes related to SkinScan3D implementation in routine clinical settings. Data triangulation will be applied to cross-validate findings from interviews and direct observation to ensure rigor and validity of the qualitative analysis.

For the cost analysis, we will summarize data to estimate the total program cost of SS3D per patient and per visit, excluding research costs. Costs will be broken down by the categories in Table 2 to identify key cost drivers.

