### Who will be included in each analysis {27b}

All enrolled patients with complete paired measurements will be included. Analysis for Objective 1 will be at the lesion level (up to 150 lesions from 50 participants). For Objective 2, the usability and implementation outcome analyses will include all providers who completed the relevant questionnaires. The cost analysis will include all patients enrolled during the study period.

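### The primary reproducibility comparison goes to whichever CCC point estimate is higher, with no interval on the difference, so even two equally reproducible methods yield a verdict

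*Protocol article*

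**What the plan says.** Under Outcomes {16}, the first primary outcome for Objective 1 is the inter-rater CCC of projected lesion area in mm². On how it is obtained: "The CCC will be calculated separately for SS3D and for the ruler-based method". Two clinicians measure the same three lesions per participant. The decision rule follows: "The method with the higher CCC will be considered the more reproducible".

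Statistical methods {27a} repeats this rule and ranks the second primary outcome, R-squared, in the same way: "The method with the higher CCC will be considered the more reproducible, and the method with R-squared closer to 1" is taken as the more accurate.

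Sample size {19} rests on "the expected width of a 95% confidence interval (CI) for the concordance correlation coefficient for a given number of lesions examined", with lesion area as measured by SS3D. It concludes that "with at least 50 participants with 3 lesions each (150 lesions), we will get a precise estimate of the CCC". Section {27b} sets the unit of analysis: "Analysis for Objective 1 will be at the lesion level (up to 150 lesions from 50 participants").

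Section {5} states that the analysis plan is contained in {27a} to {27d}, so this rule is the plan itself and not a placeholder for one.

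**The concern.** The question is comparative. Section {9b} says the comparison with the ruler will establish whether SS3D is superior in reproducibility and accuracy. The quantity that answers it is the difference between two correlated CCCs estimated on the same lesions. The plan attaches no uncertainty to that difference and turns its sign directly into a conclusion. Lesion area is effectively continuous, so a tie is close to impossible and every data set produces a verdict.

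The other planned statistics do not fill the gap. Table 1 concerns one CCC. The Bland-Altman limits, mean absolute error and root mean square error are described as capturing differences in area between methods, not the difference in reproducibility.

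The stake is the headline claim. The abstract and the Discussion link superior reproducibility to earlier decisions about chemotherapy and to adoption in trials and routine care. A result that chance alone would give half the time should not carry that.

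**Working it through.** **1. Reproduce the protocol's own figure.** For one CCC, with equal means and variances for the two clinicians, the Fisher-z interval is tanh(atanh(CCC) ± 1.96/√(n − 2)). At n = 150, 1.96/√148 = 0.161.
- CCC 0.8: atanh = 1.099, giving 0.734 to 0.851 (Table 1: 0.73 to 0.85).
- CCC 0.9: atanh = 1.472, giving 0.865 to 0.926 (Table 1: 0.86 to 0.93).

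All six entries of Table 1 reproduce to two decimals. The table is arithmetically sound, but it treats lesions as independent and describes one method.

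**2. Rough size of the noise in the difference.** If the two CCCs were independent, the SD of their difference would be about (1 − CCC²) × √(2/148) = (1 − CCC²) × 0.116. That is 0.36 × 0.116 = 0.042 at CCC 0.8 and 0.19 × 0.116 = 0.022 at CCC 0.9. Sharing the same lesions lowers this; clustering and skewness raise it.

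**3. Simulation on a normal scale.** 20,000 trials per setting; 50 participants × 3 lesions; two clinicians; both methods on the same true sizes; independent errors; no clinician bias. The within-participant correlation of true size and of error is not in the protocol and was set to 0, 0.3 and 0.5.

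| True CCCs | Trials with a verdict | First method ranked higher | SD of difference | 95% half-width |
|---|---|---|---|---|
| 0.80 v 0.80 | 100% | 50% | 0.033–0.041 | 0.065–0.080 |
| 0.90 v 0.90 | 100% | 50% | 0.017–0.021 | 0.033–0.040 |
| 0.82 v 0.80 | 100% | 71–74% | 0.031–0.039 | 0.061–0.076 |

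With equal CCCs, the observed gap exceeds 0.03 in 36–46% of trials at 0.8 and in 7–14% at 0.9. At 0.82 against 0.80, the worse method is chosen in 26–29%.

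**4. The planned scale, raw mm².** Here area is assumed lognormal with log-SD 0.8 to 1.0, and within-participant correlation is 0.5 for true size and 0.3 for error. None of these values is in the protocol.

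| SS3D v ruler (true) | SS3D ranked higher, log scale | SS3D ranked higher, raw mm² |
|---|---|---|
| Equal | 50% | 50% |
| 0.88 v 0.90 | 15–16% | 31–36% |
| 0.78 v 0.80 | 29–31% | 38–42% |

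The SD of the difference is 0.018–0.037 on the log scale. On raw mm² it is about 0.04–0.10 when the stated CCCs are set on the mm² scale, and about 0.06–0.14 when they are set on the log scale, which gives lower raw CCCs. Either way, gaps of several hundredths lie within sampling error.

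**5. Behaviour of the remedy.** Participant-level percentile bootstrap of the paired difference, under the same assumptions; ranges cover repeated runs.

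| | Log scale | Raw mm² |
|---|---|---|
| Coverage of the 95% interval | 92–94% | 88–93% |
| Lower limit > 0, equal CCCs | 3–4% | 4–7% |
| Lower limit > 0, 0.90 v 0.85 | 64–67% | 27–33% |
| Lower limit > 0, 0.90 v 0.80 | 98–99% | 53–67% |

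The nominal one-sided rate is 2.5%. A separate two-sided check on the normal scale, with correlation 0.3 and 400 trials, gave 7–10% against a nominal 5%.

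**The case against.** The strongest defence is that the study calls itself exploratory in {12}, {28b} and {28a}. It states no alpha, power or margin, and it justifies its size by precision. On that reading the rule is a descriptive ranking, and a controlled error rate is a confirmatory standard it never claimed to meet. Nothing forbids reporting intervals as well. This softens the consequences but does not remove the flaw. An exploratory study would report estimates with their uncertainty, whereas this plan prescribes a verdict and {9b} says the comparison will determine superiority.

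A second objection is that the percentages rest on assumed correlations and skewness, and that the log-scale figures describe an analysis the protocol does not plan. That is fair, and it is why both scales are shown. The central result, a verdict every time with a 50:50 split under equality, needs none of those values.

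A third objection stands in part. On skewed mm² data the bootstrap is somewhat liberal and often inconclusive, even for a true gap of 0.10. The log-scale chances of a conclusive result should therefore not be quoted for the planned mm² analysis.

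**Conclusion.** The concern holds and should be fixed before results are known. As written, the primary reproducibility conclusion has no controlled error rate. Under equality, SS3D is named more reproducible about 50% of the time. With SS3D truly 0.02 worse, it is still named better in roughly 15–31% of trials on a log scale and 31–42% on raw mm². Those last ranges depend on assumed clustering (0.5 for true size, 0.3 for error), lognormal areas and no clinician bias; the result under equality requires only that the methods be interchangeable. Table 1 is correct for what it states but does not size this comparison.

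**What to change.** Replace the rule in Outcomes {16} and Statistical methods {27a} with wording such as:

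> The primary estimand is CCC(SS3D) minus CCC(ruler), on lesions measured by both clinicians with both methods. Its 95% confidence interval is obtained by bootstrap resampling of participants, keeping each participant's lesions, clinicians and methods together. SS3D is called more reproducible only if the lower limit exceeds 0, and the ruler only if the upper limit is below 0; otherwise the methods are reported as not shown to differ.

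Three accompanying changes are needed:
- State the expected width of this interval beside Table 1, with the assumed clustering and skewness. On the normal model the half-width is 0.065–0.080 at CCC 0.8 and 0.033–0.040 at 0.9; on mm² it will be wider. Fix the scale and the bootstrap variant in advance, since the simple percentile form is slightly liberal.
- Remove the matching point-estimate ranking for R-squared, which has the same defect.
- Align {27c}, which drops an unmeasurable lesion only from the affected method's analysis, so that both CCCs use a common set of lesions.

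The cost is a few lines of text and a standard computation, with no added patients or procedures. The real downside is more inconclusive results: on skewed mm² data, a true 0.90 against 0.85 would be shown in only about 27–33% of trials. Trial status says Uganda began recruiting on 1 April 2026 and Kenya has not started, so the change can still be made before the data could influence it.

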##### Secondary outcomes:

(1) Bland-Altman agreement plots comparing the two methods. (2) Mean absolute error and root mean square error. (3) Exploratory analyses of correlation between area measurements and changes in lesion height and color, stratified by lesion morphology (flat, nodular, plaque) and size (less than 1 cm versus 1 cm or greater).

#### Objective 2 (Clinical Validation)

##### Primary outcome:

System Usability Scale (SUS) composite score for SS3D, measured after device use. The SUS is a validated 10-item questionnaire yielding a single score from 0 to 100, with scores above 68 considered above average.^11^

##### Secondary outcomes:

(1) Acceptability of Intervention Measure (AIM), Intervention Appropriateness Measure (IAM), and Feasibility of Intervention Measure (FIM) scores.^12^ (2) Time-and-motion data characterizing clinic workflows, task-shifting, and time associated with clinic visits. (3) Implementation cost per patient and per visit, estimated using activity-based micro-costing.^13^

### Harms {17}

The risks posed to participants are minimal, as the study involves non-invasive imaging and questionnaire completion. There is a very low risk of loss of privacy if there was a breach in data security. We have not experienced such a breach with our current systems that feature limited access to personnel and password-protected authentication among approved users. Patients may also experience emotional discomfort when talking about their skin conditions. To mitigate, we will train our interviewers to observe participants for discomfort, minimize probing when discomfort is perceived, and express empathy to support the participant. All adverse events observed or reported will be documented and reported to the relevant ethics committees according to their requirements.

### Participant timeline {18}

#### Objective 1

Each participant will complete a single study visit. At this visit, written informed consent will be obtained, demographic and clinical data collected, and three marker lesions identified. Two clinicians will independently measure the three lesions using both the ruler-based method and SS3D. The total additional time for study procedures is estimated at 15 to 30 minutes beyond the routine clinic visit.

#### Objective 2

During months 1 to 3 (control period), providers will measure KS lesions using the standard ruler-based method. Providers will also complete training on SS3D during this period. Thereafter, self-administered survey questionnaires will be used to gather information on usability, acceptability, appropriateness, and feasibility of the SS3D intervention. During the intervention period, providers will switch to using SS3D for KS lesion measurements. Time-and-motion observations and cost data collection will occur throughout both periods. Semi-structured interviews with a purposive sample of providers will then be conducted after the intervention period.

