### Trial design {12}

PRIME-KS uses a two-objective sequential design within an exploratory framework. Objective 1 is a cross-sectional diagnostic reproducibility and accuracy study comparing SS3D with ruler-based KS lesion measurement. It uses a paired design in which two clinicians independently measure three lesions per participant using both methods. Objective 2 is a non-randomized before-and-after pilot study in which providers first use the manual ruler-based method for three months, then switch to using SS3D, allowing within-provider comparison of implementation outcomes. There is no randomization; the study is a prospective single-arm observational study to validate accuracy, reproducibility, and clinical workflow integration.

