#### Objective 2 measurements

Measurements for Objective 2 will happen in two phases. In phase 1, providers will first measure KS lesions using the manual ruler-based method as per usual standard of care for the first three months. During this time, providers will be trained on use of the adapted SS3D device and protocols. Thereafter, we will administered survey questionnaires to gather information on usability, acceptability, appropriateness, and feasibility of the SS3D intervention. We will also conduct direct observation for workflow mapping, time-and-motion studies, and micro-costing within implementing clinics. Using the System Usability Scale (SUS)^11^, a reliable, well-validated ten-item scale for measuring usability of hardware, software, and applications, we will collect information from providers on multiple aspects of system usability, including need for support, training, complexity. Data regarding acceptability, appropriateness, and feasibility of integrating the device into routine workflows will be collected using the following validated instruments: the Acceptability of Intervention Measure (AIM), Intervention Appropriateness Measure (IAM), and Feasibility of Intervention Measure (FIM)^12^. We will collect data on clinic workflows including any task-shifting, and time associated with clinic visits for patients and providers through time-and-motion studies. Implementation costs will be documented using activity-based micro-costing techniques ^13^.

We will select a random sample of providers to undergo semi-structured interviews to enrich findings from the quantitative measures above.

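### The Objective 2 primary outcome (SUS) has no consistent time point: its definition puts it after device use, while the timeline lists the survey before providers switch to SS3D

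*Protocol article*

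**What the plan says.** Outcomes {16} gives the Objective 2 primary outcome as "System Usability Scale (SUS) composite score for SS3D, measured after device use". No month, visit or minimum exposure is attached.

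Participant timeline {18} opens Objective 2 with the ruler phase: "During months 1 to 3 (control period), providers will measure KS lesions using the standard ruler-based method". Training on the new device falls inside those same months. The questionnaires are the next step listed: "Thereafter, self-administered survey questionnaires will be used to gather information on usability, acceptability, appropriateness, and feasibility of the SS3D intervention". The changeover is described only after that step: "During the intervention period, providers will switch to using SS3D for KS lesion measurements". The section then says that time-and-motion and cost data are gathered in both periods, and places the provider interviews explicitly after the intervention period.

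Objective 2 measurements in {25a} announces two phases but labels only the first, the ruler months with training. It continues: "Thereafter, we will administered survey questionnaires to gather information on usability, acceptability, appropriateness, and feasibility of the SS3D intervention".

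Trial design {12} describes the switch from ruler to SS3D as "allowing within-provider comparison of implementation outcomes". On respondents, Sample size {19} says "All providers will complete quantitative surveys". Statistical methods {27a} grades SUS against a fixed score of 68 and summarises AIM, IAM and FIM descriptively.

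**The concern.** SUS is a user's rating of a system, so its meaning depends on how much the user has handled that system. Objective 2 is about workflow in real-world settings. A rating given after training and before the first routine SS3D measurement describes the training session. A rating given at the end of the SS3D period describes clinic use. These are different quantities, and the protocol's sections point to different ones.

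The protocol's Discussion itself expects that new users may not fully understand the device early on and may give unsuitable answers during initial implementation. A post-training survey falls at or before that stage. If sites read the text differently, they would also survey providers at different levels of experience, and the planned description by site would mix site with exposure. A missed time point cannot be recovered later.

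A smaller, related point concerns {12}. It gives a within-provider comparison as what the before-and-after design allows, but the four questionnaire scores are planned for SS3D only.

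**Working it through.** No arithmetic applies. The document states no expected SUS mean, standard deviation, precision target or number of survey respondents, so there is no figure to reproduce. The check sets the sections side by side.

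**Timing of the questionnaires**

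| Section | What it fixes about survey timing |
|---|---|
| {16} | After the device has been used; no time point |
| {18} | After the ruler and training months; listed before the switch to SS3D |
| {25a} | After the ruler and training months; no SS3D period placed before or after the survey |

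The sequence written in {18} is:

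1. Months 1 to 3: ruler measurement, with SS3D training.
2. Questionnaires about SS3D.
3. Providers switch to SS3D.
4. Interviews after the intervention period.

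The interviews are tied explicitly to the end of the SS3D period and the questionnaires are not. Taken in this order, step 2 agrees with {16} only if handling the device in training counts as device use, and nothing in the document says that it does. {25a} cannot break the tie: its second phase is never labelled, and its only time marker is that the surveys follow the ruler months.

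**Which outcomes have a ruler-period value**

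| Objective 2 outcome | Collected in the ruler period? | Collected for SS3D? |
|---|---|---|
| SUS | No | Yes |
| AIM, IAM, FIM | No | Yes |
| Time-and-motion | Yes | Yes |
| Cost | Yes | Yes |

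A within-provider before-and-after comparison is therefore possible for time-and-motion and cost, and not for the four questionnaire scores. {27a} describes no before-versus-after contrast for any outcome, and its cost analysis targets SS3D alone.

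**Who responds**

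{25a} and {27b} make providers the SUS respondents. The 100 in {19} is the patient rollout (50 + 25 + 25). The limit of 10 providers per clinic in {19} belongs to the semi-structured interviews, so it does not give a survey sample size. The precision of the SUS mean cannot be derived from the document.

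**The case against.** The strongest reply is that the word *Thereafter* sets only a lower bound. It says the surveys come after month 3, and since SS3D use also follows month 3, a survey during or after that use satisfies it. The paragraph in {18} is not strictly chronological either: the time-and-motion sentence follows the switch but covers both periods. In {25a}, the surveys can quite naturally be read as part of the unlabelled second phase. And {16}, which defines the outcome, has the right sense.

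This stands as far as it goes. A reader might infer that the protocol schedules SUS before any SS3D use; no section says so outright, and {16} says the opposite. What remains is a conflict between the definition and the written order of the timeline, with nothing elsewhere to resolve it.

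A reader might also infer that the comparison promised in {12} cannot be made at all. That goes too far, because time-and-motion and cost are implementation outcomes collected in both periods.

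Nor is the absence of a ruler-period SUS a defect in the primary outcome. That outcome is a descriptive SS3D score read against 68, in a study that calls itself exploratory, and {25a} presents SUS as a scale for hardware, software and applications, which does not obviously fit a ruler. Requiring a lower confidence limit above 68 would likewise add a confirmatory rule that the design does not need. {27b} already makes clear that the analysis covers providers who completed the questionnaires.

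**Conclusion.** The timing of the Objective 2 primary outcome is internally inconsistent and needs to be fixed before the first survey is given. If {18} is followed in its written order, SUS, AIM, IAM and FIM from every responding provider would reflect training exposure rather than routine use. If it is read in line with {16}, they would not. The protocol does not say which, and the size of any resulting difference in scores cannot be estimated from it.

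The conclusion rests on two readings: that sites would treat the order of sentences in {18} as the order of events, and that device use in {16} means use on patients rather than handling in training. If either fails, what is left is an undefined time point for a primary outcome.

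The statement in {12} is too broad rather than wrong: it holds for time-and-motion and cost, and not for the four questionnaire scores.

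**What to change.** - In {16}, {18} and {25a}, state that SUS, AIM, IAM and FIM for SS3D are administered at the end of the SS3D intervention period and that this is the primary assessment. Label any survey given after training a baseline.
- In {12}, limit the within-provider comparison to the outcomes measured in both periods, namely time-and-motion and cost.
- In {27a}, report the SUS mean with a 95% confidence interval and the number of responding providers.

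A ruler-period questionnaire and a lower-limit criterion against 68 are options the sponsor may consider. Neither is needed to correct the plan.

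The cost is small: one survey moves, its results arrive later, and the wording goes through the amendment process in {31}.
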